### Randomization

Block randomization in multiples of three will be carried out at each study site by opening sealed envelopes containing computer-generated block randomization numbers, with block sizes of six and nine to ensure roughly equal numbers of patients in each arm at any point in the study. The patients and medical team will not be blinded to the intervention with only the statistician performing the analyses being blinded.

### Patient selection and data collection

Eligible patients will be identified, counselled and enrolled by gynaecologists at each study centre. Before entry into the study the gynaecologist will explain to a potential patient the aims, methods, reasonably anticipated benefits and potential hazards of the study. Patient information sheets will be distributed to eligible patients and a research assistant will be available for a more detailed explanation. They will also explain to patients the potential benefit of extended long-term follow-up that would otherwise not be available and other intended benefits to the healthcare system as well as the country by participation in this research. After sufficient information, informed written consent will be obtained. Research assistants will assign enrolled participants to have either a TLH, NDVH or a TAH (Fig. 1). Patients who decline participation in the study will have standard treatment (TAH).

A preoperative questionnaire on general information, quality of life, pelvic organ function (urinary, vaginal and sexual and bowel function) and costs incurred up to surgery would be filled in by the patient while another on relevant medical information would be filled by a research assistant a day prior to surgery. Standard techniques of TLH, TAH and NDVH would be followed [15, 16]. The decision to convert to laparotomy at TLH or NDVH would be at the discretion of the primary surgeon.

Data on operative time, complications, instruments and medications used and staff allocation during surgery will be entered into a data collection sheet immediately after surgery. During the postoperative period the following information will be collected by a research assistant using a datasheet; complications, pain scores and analgesic medication and investigations. A patient-filled questionnaire will obtain costs incurred by the patient due to hospital admission. The health utility scores based on paper-based EuroQoL group health-related quality of life (EQ-5D-3L) questionnaires will be estimated on day 2 and 1 week post-surgery. (A self-addressed stamped envelope along with an EQ-5D-3L form will be provided to the patient on discharge with instructions to mail the 1-week assessment).

Patients will be reviewed at 6 weeks in the gynaecology clinic and information on time to recover, health utility scores, hospital admissions, complications and investigations will be collected. Health utility scores will be estimated at 3 months by sending an EQ-5D-3L form via post along with a stamped self-addressed envelope. Patients will be reviewed at 6 months in the gynaecology clinic and information on health utility scores, pelvic organ function in addition to any complications or readmissions would be obtained. At the 1-year visit, information on pelvic organ function will be collected. The timing of assessments for each outcome is shown in Table 1.

### Description of study instruments

The validated paper-based Sinhala and Tamil EQ-5D-3L questionnaire will be used to obtain health utility scores. The EQ-5D-3L is a generic multi-attribute utility system, which assess health-related quality of life on five dimensions (mobility, self-care, usual activities, pain/discomfort, anxiety/depression) [17]. Based on the responses a woman will be placed in to one of 243 (3^5^) mutually exclusive health states, and a value for each of these has previously been estimated with ‘0’ being equivalent to dead and ‘1’ being equivalent to perfect health on a utility scale based on interviews. EQ-5D 3L questionnaires will be administered 1 day preoperatively and on postoperative day 2, 1 week, 6 weeks, 3 months and 6 months postoperatively. Each woman’s QALYs will be calculated using the utility score and the time spent on the particular health state. A utility value table specific to Sri Lanka will be used to calculate QALYs [18].

Urinary and sexual function will be assessed by the validated Sinhala and Tamil translations of International Consultation on Incontinence Modular Questionnaire on Female Urinary Tract Symptoms (ICIQ-FLUTS) and Incontinence Modular Questionnaire on Vaginal Symptoms ICIQ-VS which were obtained from the International Consultation on Incontinence (ICI) [19–21]. Bowel symptoms will be assessed by a questionnaire based on a study done by Tharkar et al. [22]. These questionnaires will be used preoperatively, 6 months and up to 1 year post-hysterectomy to detect changes in pelvic organ function.

Postoperative pain evaluation will be done using numeric pain rating scale (NRS) [23], asking the patient to indicate the intensity of current, best, and worst pain levels over the past 24 hours on a scale of 0 (no pain) to 10 (worst pain imaginable). The average of the three ratings; average, best, and worst will be used to represent the patient’s level of pain over the previous 24 hours. To allow direct comparison of pain medication a modified World Federation of Societies of Anaesthesiologists (WFSA) analgesic ladder will be used [24].

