**Fig. 2 Fig2:**
[figure not shown]
Schedule of enrolment, interventions and assessments. ^#^- preoperative assessment done 1-day prior to surgery. *-via postal assessment

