### Compliance issues

Participants can exit the trial at any given point. Exit is defined as exiting the trial altogether or wanting another procedure different from the one allocated by randomization. If they exit after randomization but prior to surgery it will be mentioned but they will not be included in the analysis. However, if they wish to exit the trial after surgery, we will retain their data and their permission to access healthcare records unless consent for these activities is explicitly withdrawn. We will also actively try to minimize actual loss to follow-up by contacting patients through available contact information and access to information in hospital. We feel the rate of non-compliance will be low as well-motivated women will participate in a study of this nature. We also feel that it will be the same for participating gynaecologists as competent and well-motivated individuals who want to help answer the research question were chosen. Divergence from a pre-specified trial arm will be documented with reasons and included in the analysis of the originally allocated trial arm.

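### As the text reads, the only baseline for pelvic function and EQ-5D-3L is self-reported the day before surgery by women who already know their allocated route

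*Protocol article*

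**What the plan says.** Description of study instruments sets the first utility measurement: "EQ-5D 3L questionnaires will be administered 1 day preoperatively and on postoperative day 2". The legend of Fig. 2 agrees: "preoperative assessment done 1-day prior to surgery". The urinary, vaginal/sexual and bowel questionnaires are given before surgery, at 6 months and up to 1 year, "to detect changes in pelvic organ function".

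Patient selection and data collection first describes counselling and written consent, then says "Research assistants will assign enrolled participants to have either a TLH, NDVH or a TAH", and in the next paragraph turns to the preoperative forms. One form covers general information, quality of life, pelvic organ function and costs: "costs incurred up to surgery would be filled in by the patient while another on relevant medical information would be filled by a research assistant". No earlier baseline is described.

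Randomization says "The patients and medical team will not be blinded to the intervention". Compliance issues covers women who leave before the operation ("If they exit after randomization but prior to surgery") and counts as an exit a wish for a procedure other than the allocated one.

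**The concern.** A baseline score should be fixed before anyone can know the allocation. Here the reference appears to be an open self-report given on the eve of a known operation. Expecting an abdominal, vaginal or laparoscopic procedure could change how a woman answers items on anxiety, pain or symptoms, and could do so differently by arm. Such a score is a post-randomisation measurement. If it is subtracted from follow-up or used as a covariate, part of any arm-specific shift passes into the treatment contrast.

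At stake is the secondary objective on urinary, sexual and bowel function, which is also part of the trial hypothesis, together with any utility analysis that adjusts for baseline. This is a matter of conduct. A later analysis plan cannot recover a pre-allocation score that was never collected.

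**Working it through.** The article gives no figure on this point. Its computed sample size of 49 per arm concerns time to recover and is not involved. The check is therefore a reading of the sections together, followed by illustrations on assumed values.

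**Order of events**
1. Patient selection and data collection describes consent, then assignment, then the preoperative forms.
2. Description of study instruments and the legend of Fig. 2 place the preoperative assessment one day before surgery.
3. Compliance issues provides for an interval between randomisation and surgery in which a woman may want another route. She can only want a different route if she knows her own, so the allocation can be known before surgery.
4. Randomization confirms that women are not blinded.
5. No sentence requires the forms to be complete before the envelope is opened.

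Post-allocation completion is the natural reading. It is not stated in words, and the schedule figure that could settle it is not shown.

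**Which outcomes use the baseline**
- Pelvic function: yes, since the instruments are meant to show change.
- QALYs: Description of study instruments defines them as utility multiplied by time in the health state, with no change from baseline.
- Costs: Economic evaluation accumulates them from first clinic presentation to 6 months. Preoperative costs are a component of the total and not a reference value.
- Time to recover (primary): no questionnaire score enters.

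**Effect on pelvic-function scores** (shift and slope are assumptions)

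Let knowledge of the route shift the baseline of one arm by s, in SD units, leaving follow-up unchanged. Let b be the slope of follow-up on baseline, equal to the correlation when the SDs are equal.
- Change score: bias = −s. For s = 0.1 to 0.3, the size is 0.1 to 0.3 SD.
- Baseline-adjusted comparison: bias = −b × s. For b = 0.3 to 0.7, the size runs from 0.3 × 0.1 = 0.03 SD to 0.7 × 0.3 = 0.21 SD.
- Follow-up-only comparison: bias from this source = 0.

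**Effect on QALYs** (utility shift is an assumption)
- Plain area under the curve, assuming linear interpolation from day −1 to day 2: shift × 1/2 × 3/365.25. A shift of 0.05 gives 0.0002 and a shift of 0.20 gives 0.0008.
- Regression adjusted for baseline utility, over half a year with an assumed slope of 0.3 to 0.6: 0.05 × 0.3 × 0.5 = 0.0075 to 0.05 × 0.6 × 0.5 = 0.015. The article does not state this adjustment.
- For scale, 7 days' faster recovery at an assumed utility gap of 0.2 is worth 7/365 × 0.2 = 0.0038 QALY.

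**The case against.** **The order is inferred.** The section on selection and data collection is not strictly chronological: it mentions women who decline participation after it mentions assignment. An envelope opened after the day-before forms would also fit the interval in Compliance issues. This stands, and it is why the point is put as what the text implies. The first remedy is a sentence stating the order.

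**Few outcomes depend on the baseline.** A reader might infer that every comparison in the trial is compromised, costs and QALYs included. The documents do not support that, since neither is a change from baseline and the primary outcome uses no baseline score. A reader might also set 0.0075 to 0.015 against 0.0038 and conclude that the bias could exceed the whole benefit of faster recovery. That needs a baseline adjustment the article does not state. With utility times time, the same 0.05 shift is worth about 0.0002, roughly 5% of 0.0038.

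**Even for pelvic function, no change score is specified.** Data analysis names Kaplan–Meier and Cox methods for these outcomes and mentions no baseline covariate. This also stands in part. The link to change rests on one sentence in Description of study instruments, which is nonetheless the declared purpose of collecting the preoperative score.

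**Later questionnaires are open self-reports too.** True, and the Discussion acknowledges the lack of blinding. Moving the baseline removes only the part of the exposure that can be avoided.

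**Women who exit before the day-before visit have no baseline.** Their exclusion from analysis comes from Compliance issues and not from the questionnaire timing. Earlier forms would only allow these women to be described.

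**Conclusion.** The concern holds in a limited form. As the text reads, the only baseline for urinary, vaginal/sexual and bowel function and for EQ-5D-3L follows open allocation. A differential shift would pass in full into a change in pelvic function, and in proportion to the slope into any baseline-adjusted comparison, including utilities if they are adjusted. The 0.1 to 0.3 SD and 0.03 to 0.21 SD figures are illustrations on assumed shifts and slopes. The documents allow neither the size nor the direction of a bias to be derived, and they do not show that one occurs.

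Time to recover, accumulated costs and a plain area-under-the-curve QALY are essentially unaffected. The point therefore concerns a stated secondary objective and does not threaten the main result. It is worth acting on because the protection is cheap and cannot be supplied later by analysis.

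**What to change.** State in Randomization and in Patient selection and data collection that the EQ-5D-3L and pelvic-function baseline forms are completed after consent, and that the research assistant opens the envelope only once they are handed in. If sites already work this way, that sentence closes the point.

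Keep costs up to surgery on a day-before sheet, since they cannot be complete earlier. If a utility value close to surgery is wanted as the start of the QALY curve, repeat the EQ-5D-3L on that sheet.

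Trial status reports randomisation from 1 August 2016, with recruitment ongoing. For women already enrolled, record the dates of allocation and of the preoperative questionnaire, and report a follow-up-only comparison of pelvic function as a sensitivity analysis.

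The cost is a wording change, a reordering of existing steps by the same staff, and one short extra sheet. The downsides are a baseline somewhat further from surgery and baseline timing that differs between early and late participants.

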### Data security and cleaning

The completed questionnaires and data collection sheets will be collected and entered locally in an ongoing computer database at each centre. Data will be stored in password-protected folders. An independent data monitoring committee comprising of staff from the computer centre of the Faculty of Medicine, University of Kelaniya will undertake regular checks and monitoring to ensure compliance and enhance accuracy at both centres.

### Compliance issues

Participants can exit the trial at any given point. Exit is defined as exiting the trial altogether or wanting another procedure different from the one allocated by randomization. If they exit after randomization but prior to surgery it will be mentioned but they will not be included in the analysis. However, if they wish to exit the trial after surgery, we will retain their data and their permission to access healthcare records unless consent for these activities is explicitly withdrawn. We will also actively try to minimize actual loss to follow-up by contacting patients through available contact information and access to information in hospital. We feel the rate of non-compliance will be low as well-motivated women will participate in a study of this nature. We also feel that it will be the same for participating gynaecologists as competent and well-motivated individuals who want to help answer the research question were chosen. Divergence from a pre-specified trial arm will be documented with reasons and included in the analysis of the originally allocated trial arm.

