### Data analysis

All randomized patients will be included in the analyses. A single principal analysis will be done comparing the three arms (TAH, NDVH and TLH) 12 months after the last woman has had her operation. The fact that the trial will be conducted at two centres will be taken into account during data analysis.

A Kaplan–Meier survival analysis will be done for the primary outcome which is time to recover following hysterectomy. The end-point is the actual time to recover. It will be assessed and documented at the 6-week clinic visit. Patients who have not recovered by 6-weeks will be followed-up beyond 6-weeks to detect complications and the actual time to recover. Post hoc pairwise analysis between TAH, NDVH and TLH will be done using COX regression.

Other outcomes that need follow-up; QALYs, urinary, vaginal and bowel functions will also be analysed using Kaplan Meier survival analyses. The end point for QALYs is 6-months while for urinary, vaginal and sexual function it is 1-year. Patients who do not complete follow-up in these secondary outcomes will be right censored up to their respective end-points. Post hoc pairwise analysis between TAH, NDVH and TLH will be done using COX regression. The other outcomes; operative time, anaesthesia time, postoperative hospital stay, cost, pain scores and blood loss will be analysed using Kruskal-Wallis test with post hoc comparisons. The complications will be described for each category. A fully specified Statistical Analysis Plan will be provided before opening the database.

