## Discussion

Studies in low-resource settings are hampered by financial limitations and feasibility in terms of time and collection of good quality accurate data. This protocol considers many relevant aspects concerned with the comparison of total abdominal, non-descent vaginal and total laparoscopic hysterectomy in one study for a lower-middle-income country where evidence on surgical outcomes especially in the form of randomized controlled trials are hard to come by. We believe these reasons make this protocol appealing for other researchers in similar settings.

As this is a multicentre study the involvement of multiple surgeons is inevitable and this can raise the issue of various skill levels and affect the outcome of surgery rather than a single operator. Although the issue of multiple surgeons is a limitation to the study itself, the generalisability of the results to the rest of the country would be more in our design of a pragmatic multicentre study involving multiple surgeons for each method rather than a single-centre study with a single surgeon for each method. In a study of this nature, it would not be possible to blind the patients nor the surgeons as the scars are distinct in each method. Although this is a limitation it is unavoidable and only the statistician will be blinded. The use of objective questionnaires, for patients’ as well as for assessors will also help to minimize bias [12].

The primary outcome, of time to resume usual activities, could be subject to recall bias. As it is a patient-reported outcome it has the advantage of being the best estimator of convalescence in the eyes of patients despite being subjective. Pelvic organ function is also assessed through patient-filled questionnaires as there is no objective method of assessing postoperative pelvic organ function. Although patient-reported outcomes can be subjective, validated questionnaires such as the ones used in this study make these assessments more valid and reliable. These questionnaires are the only available, non-invasive and generically applicable tools that can be used in low-resource settings.

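### Women who exit between randomisation and surgery, including those who want another procedure, are dropped under one rule and kept under another, and the exclusion permits selection by arm

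*Protocol article*

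**What the plan says.** The Compliance issues section of the protocol article gives a definition and three handling rules.

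- Definition: "Exit is defined as exiting the trial altogether or wanting another procedure different from the one allocated by randomization".
- Exit before surgery: "If they exit after randomization but prior to surgery it will be mentioned but they will not be included in the analysis".
- Exit after surgery: "if they wish to exit the trial after surgery, we will retain their data", unless consent is explicitly withdrawn.
- Departure from the allocated arm: "Divergence from a pre-specified trial arm will be documented with reasons and included in the analysis of the originally allocated trial arm".

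The Data analysis section opens with a rule that has no exceptions: "All randomized patients will be included in the analyses".

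Two other statements bear on the point. The Randomization section says: "The patients and medical team will not be blinded to the intervention with only the statistician performing the analyses being blinded". The section on patient selection and data collection says that women who decline the study receive TAH as the standard treatment.

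**The concern.** The article fixes two analysis sets that cannot both be used. One drops every woman who exits between randomisation and surgery. The other contains everyone randomised.

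The exclusion rule is also the weaker of the two. It acts on a decision made after randomisation by women who know their allocation, and by definition that decision includes rejecting the allocated route. The arms are not symmetric in this respect, because TAH is what women receive by default outside the trial. Refusal could therefore differ between arms, both in how often it happens and in who refuses. If it does, the women left in each arm are no longer comparable. The primary outcome, time to recover, is exposed to this. So are QALYs, costs and the ICERs computed from them. The Discussion notes that time to recover is patient-reported, so preferences that drive refusal may also be related to the recovery time a woman reports.

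For most switchers nothing forces the loss. A woman who has a different route of hysterectomy still has an operation, a 6-week visit and a recovery time.

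**Working it through.** **Where each rule sends a given woman**

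| Case | Pre-surgery exit rule | All-randomised rule | Divergence sentence |
|---|---|---|---|
| Allocated TLH, asks for TAH before surgery | Out | In | In allocated arm, if the sentence covers patient requests |
| Leaves the trial altogether before surgery | Out | In | Not addressed |
| TLH or NDVH converted to laparotomy at operation | Does not apply | In | In allocated arm |
| Leaves after surgery | Does not apply (data retained) | In | Not addressed |

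The first two rows conflict however the divergence sentence is read. In the first row that sentence may add a further conflict.

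**The plan's own sample size**

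Inputs from the Sample size calculation section: difference 7 days; SD 9.5 (TAH) and 8.5 (VH); two-sided alpha 0.01; power 80%; loss 20%.

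- Pooled SD = √[(9.5² + 8.5²)/2] = √81.25 = 9.014.
- These inputs give 39 evaluable women per arm.
- 39/0.8 = 48.75, so 49 per arm and 147 in total.

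This reproduces the stated figure. Analysing all randomised women by allocation leaves it unchanged.

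**Possible shift in an arm's mean**

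If a share e of one arm is excluded and those women differ by s days from the women retained, the arm's mean shifts by e × s. The article gives neither quantity, so both are assumed.

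- e = 5%, s = 5 days: 0.05 × 5 = 0.25 days, or 0.25/7 ≈ 4% of the target difference.
- e = 15%, s = 5 days: 0.15 × 5 = 0.75 days, or 0.75/7 ≈ 11%.
- e = 15%, s = 10 days: 0.15 × 10 = 1.5 days, or 1.5/7 ≈ 21%. This is an extreme bound, because 10 days exceeds each SD the article cites (9.5, 8.5 and 7.5).

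These are shifts in means. The planned primary analysis is Kaplan–Meier with Cox regression, so the percentages do not carry over directly to a hazard ratio.

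**Power, if exclusions come on top of the planned 20% loss** (difference 7, SD 9.014, alpha 0.01)

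- 39 evaluable per arm: 80.3%.
- 35 per arm: 74.9%.
- 31 per arm: 68.5%.

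**Dilution if switchers are kept in their allocated arm**

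Assume 15% of an arm switches to TAH and recovers as TAH patients do, using the cited means.

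- VH against TAH: 0.15 × (28.1 − 21.3) = 0.15 × 6.8 ≈ 1.0 day.
- LAVH (the cited laparoscopic figure) against TAH: 0.15 × (28.1 − 19.7) = 0.15 × 8.4 ≈ 1.3 days.

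**The case against.** The best defence concerns the divergence sentence. It follows a remark on the compliance of the participating gynaecologists, and the article elsewhere leaves conversion to laparotomy to the surgeon's discretion. It can therefore be read as covering only surgeon-driven or intraoperative departures, with patient choice before surgery handled separately as exit. A reader might infer that three rules are in certain mutual conflict. The text does not establish that. The certain conflict is between the pre-surgery exclusion and the all-randomised rule; the divergence sentence is ambiguous. The defence leaves that certain conflict untouched.

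A second defence is that the promised statistical analysis plan will settle the matter. It can choose between the two sets, but it could follow either and claim to comply with the article. Nor can it recover outcomes that were never collected because a woman was treated as having exited.

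A third is that non-compliance is expected to be low and that pre-surgery exits will at least be mentioned. Both are fair. The expectation is put only as a feeling, without a figure, and mentioning exits does not restore comparability.

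A reader might also infer that the results will be labelled intention-to-treat when they are not. The article never uses that term, so the charge is unsupported. Nor does it state the interval between randomisation and surgery, so it shows no fault in when the envelopes are opened.

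Finally, keeping switchers has a cost. At the same assumed 15%, the dilution is larger than the illustrative bias with a 5-day gap. That is a reason to report it openly, but it does not justify selecting on a post-randomisation choice.

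**Conclusion.** The concern holds. The article sets incompatible analysis sets, and the one in Compliance issues permits selection that depends on a known allocation. This has to be resolved because it decides who enters the primary comparison. The conclusion rests on the two rules and on the open allocation, not on the illustrative figures.

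The size of any bias is unknown. Under assumed exclusion of 5-15% of one arm and a 5-day difference, that arm's mean moves by 0.25-0.75 days. The 1.5-day figure should not be read as likely, since it needs excluded women to differ from retained women in the same arm by more than one SD. The documents do not show that refusal will differ by arm; they show that the rule allows it to and leaves the analysis unprotected.

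Not every randomised woman will have a recovery time. Women who have no hysterectomy, who withdraw consent or who are lost to follow-up will lack one. The existing retention clause covers only exits after surgery, so women who leave altogether beforehand need a provision of their own.

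**What to change.** In Compliance issues:

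- Delete the sentence excluding pre-surgery exits.
- Limit the definition of exit to leaving the trial altogether, by removing its second limb on wanting a different procedure.
- Extend the data-retention clause to exits before surgery, unless consent is withdrawn.
- Make clear that the divergence sentence covers changes of procedure before surgery as well as at surgery.

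In Data analysis:

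- State that the primary analysis includes all randomised women in their allocated arm, and that women who switch before surgery are followed with the same data sheets.
- Report by arm, with reasons, the women without a recovery time (no hysterectomy, consent withdrawn, or lost to follow-up), and add a sensitivity analysis for them.
- If wanted, keep an analysis excluding pre-surgery exits as secondary.

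The cost is a short protocol clarification, a consent or retention provision for women who leave before surgery, and the existing data sheets for switchers. The planned 147 does not change. The statistical price is dilution of the contrast by crossover, about 1.0-1.3 days under the 15% assumption. The article describes recruitment as ongoing, so at that stage switchers' outcomes could still be collected.
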